### ***8.3.2. Description of the hearing tests which will be conducted***

#### ***Consonant nucleus consonant (CNC) test***

Speech understanding in quiet will be assessed using the Dutch CNC test. This clinical test is part of the selection, rehabilitation and follow-up of CI patients in the Netherlands. Phoneme scoring (%correct) in a quiet free field listening situation at a distance of 1m to the loudspeaker will be evaluated. Two conditions will be measured: static and dynamic. Static refers to the standard clinical setting whereby the subject is sitting in a chair in front of a loudspeaker (no vestibular stimulation). Dynamic refers to a setting specifically designed for evaluation of the combined CVI function whereby the subject is walking on a treadmill (active vestibular stimulation) (see also DVA for the description of a comparable set-up).

#### ***Speech in noise (SPIN) test***

In this test sentence materials such as the Leuven Intelligibility Sentence Test (LIST), the Flemish/Dutch version of the Matrix test or number materials such as the Digits-in-noise test (DIN) are presented in noise. An adaptive procedure is applied whereby the noise is fixed at a level of 65dB sound pressure level (SPL) while the speech level is varied. This results in the speech-reception-threshold (SRT), the signal-to-noise ratio at which the subject is able to still understand 50% of the sentences

correctly. Speech and noise will be presented in free field from the same loudspeaker in front (SONO). This test can only be performed meaningfully if a minimum level of speech understanding in quiet is achieved (e.g. 40-50%).

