| Time       | 08:00 | Breakfast                        |                                  | Breakfast                                   | Breakfast                                  | Breakfast |
| 09:00      |       |                                  |                                  |                                             |                                            |           |
| 10:00      |       | Costas array-based experiment    | CI and CVI aided DVA             |                                             | Static CI aided CNC + SPIN                 |           |
| 11:00      |       | First fitting - First SCC (1/2)  | First fitting - Third SCC (1/2)  | Second fitting - Second SCC (1/2)           | Combined fitting evaluation and adjustment |           |
| 12:00      |       | Break                            | Break                            | Break                                       | Break                                      |           |
| 13:00      |       | First fitting - First SCC (2/2)  | First fitting - Third SCC (2/2)  | Second fitting - Second SCC (2/2)           | Combined fitting evaluation and adjustment |           |
| 14:00      |       | Lunch                            | Lunch                            | Lunch                                       | Lunch                                      |           |
| 15:00      |       | First fitting - Second SCC (1/2) | Second fitting - first SCC (1/2) | Second fitting - Third SCC (1/2)            | Combined fitting evaluation and adjustment |           |
| 16:00      |       | Break                            | Break                            | Break                                       | Break                                      |           |
| 17:00      |       | First fitting - Second SCC (2/2) | Second fitting - first SCC (2/2) | Second fitting - Third SCC (2/2)            | Costas array-based experiment              |           |
| 18:00      |       | VBR                              | Semi-structured interview        | Familiarization with gait and balance tests | Final overall fitting check                |           |
| 19:00      |       |                                  |                                  |                                             | Static CVI aided CNC + SPIN                |           |

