| 14:00           |                                  | DVA                             | DVA                             | DVA                             | DVA + dynamic CNC               |             |               |
| 15:00           |                                  | Break                           | Break                           | Break                           | Interview                       |             |               |
| 16:00           |                                  | Rotatory chair                  | Rehabilitation                  | Rotatory chair                  | Break                           |             |               |
| 17:00           | Perception platform E | Physiotherapeutic diagnosis     | Break                           | Costas array                    | Head impulse tests B |             |               |
| 18:00           |                                  | End-of-day check D   | End-of-day check D   | End-of-day check D   | End-of-day check D   |             |               |
| 19:00           | Dinner                           | Dinner                          | Dinner                          | Dinner                          | Dinner                          |             |               |
| Night           | Hotel                            | Hotel                           | Hotel                           | Hotel                           | Hotel                           | At home     | At home       |

| Legend for prolonged stimulation period schedule            |  |   |
|-------------------------------------------------------------|--|---|
| Time at the hotel                                           |  |   |
| Testing                                                     |  |   |
| Rehabilitation                                              |  |   |
| Time at the hospital                                        |  |   |
| Interviews                                                  |  |   |
| Habituation and device check                                |  |   |
| Free time                                                   |  |   |
| Including a short fitting check if necessary                |  | A |
| 3D HIT, fHIT, simulated 3D HIT and simulated rotatory chair |  | B |
| Impedance and UCL check                                     |  | C |
| Impedance, UCL check and VAS-based list of questions        |  | D |

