|           |                       | 1b | Safety                        | stim. weeks                                          | Sec.               |      | Questionnaires, Interviews                                      |
|           |                       |    |                               |                                                      |                    |      | (S)AE's                                                         |
|           |                       | 1c | Efficacy of 3 stim. types     | VI-ON (week 1) vs VI-ON (week 2) vs VI-ON (week 3)   | Prim.              | Main | DVA                                                             |
|           |                       |    |                               |                                                      |                    | Aux. | fHIT, 3D HIT, Torsion Swing, Gait analysis, Perception platform |
| Secondary | Rehab.                | 2a | Rehab. program                | stim. weeks                                          | Prim.              |      | Gait analysis                                                   |
|           |                       |    |                               |                                                      | Sec.               |      | Questionnaires, Interviews                                      |
|           | CI                    | 2b | Interaction between CI and VI | CI-ON/VI-OFF (baseline) vs CI-ON/VI-ON (stim. weeks) | Prim.              |      | Aided CNC, SPIN, vestibular test                                |
|           |                       |    | CI as part of VCI             | CI-ON (up to 5 years)                                | Sec.               |      | Questionnaires, Interviews                                      |
|           | Long term             | 2c | Acute efficacy                | VI-ON (up to 5 years)                                | Prim.              |      | Subset of vestibular tests                                      |
|           |                       |    |                               |                                                      |                    |      |                                                                 |

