## 10. STATISTICAL ANALYSIS

The definitive statistical plan will be constructed after data has been collected for the first patient. Below follows the general outline of the statistical plan.

A single-subject repeated measures design will be used whereby each subject acts as their own control. The outcomes of the different parameters (as described in chapter 8.1) will be bootstrapped and descriptively represented by stating mean and standard deviation, median/interquartile range and minimum/maximum values. Due to the small sample size, normality can most likely not be established, therefore non-parametric statistical tests will be performed. Confidence interval will be set at 95%. Due to the small sample size, the outcomes of this trial are not meant to serve as proof for population-wide claims. The goal of the trial is to assess feasibility of chronic vestibular stimulation with a focus on individual effectiveness (compared to within-subject control) and safety, rather than giving definitive statements on its effectiveness as a treatment for a group of patients.

Since the nature of the trial is exploratory and not confirmatory, the choice is made to include a full set of vestibular tests to assess efficacy of the CVI. The data from this trial will be used to be more rigorous in choosing outcome parameters for a future confirmatory trial with a larger population, in order to reduce multiplicity during that trial. Therefore, during this trial no structural statistical steps are taken to control the impact of multiplicities on the type 1 error. However, care will be taken to avoid combining the results of the different outcome measures into one statement on efficacy. DVA will serve as the main primary outcome for VI efficacy due to it giving objective results on the functional restoration of the VOR response pathway. All other parameters will be viewed as auxiliary.

If missing data are observed, the cause of missingness will be ascertained. When the cause of missingness is suspected to be structural, these cases will be described and excluded from analysis of the affected outcome measure. If data is concluded to be missing at random, the imputation strategy will be decided based on the nature and extend of the missingness. In this process the potential for reduced variance caused by interpolation-based imputation techniques will be taken into account. A final imputation strategy will be decided as part of the definitive statistical plan.

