##### 13.1.4. *Selectivity of the mechanism*

Due to the CVI being based on electrical stimulation, current spread will occur. As the stimulation current increases, so does current spread, which may lead to stimulation of other nerves such as facial nerves or auditory nerves. The potential for stimulating nerves outside of the inner ear is reduced due to the way the stimulation parameters are chosen, setting the maximum stimulation currents below the current at

which unwanted stimulation occurs (see chapter 8.3.2). This is the same way as current spread is reduced with a CI. Part of the study is to safely investigate the presence of interfering current spread between the cochlea and the vestibular system. The interaction between vestibular and cochlear stimulation might (temporarily) result in a reduced CI or VI performance. The patient will be informed that CI performance might be reduced during simultaneous stimulation, since this might result in a burden to the patient. This will only be the case while the VI-part is active during the VI fitting period and the prolonged stimulation period. While optimizing the VI stimulation response during the VI fitting, the goal is to minimize the interaction between CI and VI stimulation and therefore minimize this burden.

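### If VI stimulation makes the speech-in-noise threshold unobtainable, section 10 would exclude that patient from the SPIN comparison and bias SPIN towards little CI/VI interaction

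*Protocol*

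**What the plan says.** Table 6 (section 8.1.1) sets the contrast for objective 2b as "CI-ON/VI-OFF (baseline) vs CI-ON/VI-ON (stim. weeks") and lists its objective outcomes as "Aided CNC, SPIN, vestibular test". The example fitting schedule (section 3.2, Table 3) places a pair of hearing sessions on day 4: "Static CI aided CNC + SPIN" in the morning and "Static CVI aided CNC + SPIN" at the end of the day.

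Section 8.3.2 limits when SPIN is useful: "This test can only be performed meaningfully if a minimum level of speech understanding in quiet is achieved (e.g. 40-50" per cent). Below that level it does not say what is recorded. It also does not name the listening condition in which the level is judged. It allows sentence or digit materials without fixing one per patient.

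Section 13.1.4 expects an effect on hearing: "The interaction between vestibular and cochlear stimulation might (temporarily) result in a reduced CI or VI performance". Sections 1.4.6 and the Summary say the same of CI performance.

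Section 10 gives the missing-data rule: "When the cause of missingness is suspected to be structural, these cases will be described and excluded from analysis of the affected outcome measure". Imputation is considered there only for data judged missing at random. Section 10.1 compares VI-OFF with VI-ON by a Wilcoxon signed-rank test.

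**The concern.** The condition for a meaningful SPIN test is speech understanding in quiet, which the intervention under study may itself lower. If the level is judged again with the VI on, whether a patient has a VI-ON threshold depends on how much the VI harms that patient's hearing. Such a missing value is systematic, so the section 10 rule for structural missingness is the one that would naturally apply. The pairs left for SPIN would then be those with less interference.

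Objective 2b is meant to describe the extent and clinical relevance of the interaction (section 2.2). SPIN is the only speech-in-noise measure in it. A SPIN result that looks reassuring because the worst-affected patients have been set aside would mislead on that part of the question.

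**Working it through.** **1. Is there a plan figure to reproduce?** Not for this point. The protocol gives no SPIN sample size, no expected loss and no CNC distribution. Its only sample-size figure (5, section 4.4) concerns DVA.

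**2. The chain of text.**
- SPIN is a 2b outcome (Table 6) and is scheduled in both conditions (Table 3). *Stated.*
- SPIN needs a minimum level of speech understanding in quiet (8.3.2). *Stated, with the level given as an example.*
- The VI may lower CI performance (13.1.4). *Stated.*
- A patient below the level with the VI on has no usable VI-ON SRT. *Inferred. It is plausible, because 8.3.2 defines the SRT as the point of 50% correct sentences, which is hard to reach for someone near that score in quiet.*
- Such a case is excluded from SPIN (section 10). *Follows if the missingness is classed as structural.*
- The same patient stays in aided CNC, which 8.3.2 scores as percent correct with no floor. *Stated.*

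**3. What lost pairs cost the planned test.** The smallest exact two-sided signed-rank p with n pairs is 2/2^n:
- n = 8: 2/256 = 0.0078
- n = 7: 2/128 = 0.0156
- n = 6: 2/64 = 0.031
- n = 5: 2/32 = 0.0625

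With the minimum of 8 patients, losing 3 makes p < 0.05 impossible for SPIN. With the maximum of 13, losing 8 does so.

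**4. Illustration of the selection.** All inputs here are assumptions. The quiet score with VI off is normal with mean 60, 70 or 80% and SD 15. The VI-induced drop is normal with mean 5, 10 or 20 points and SD 12. Scores are clipped to 0-100, and the floor is 40 or 50%. There were 400,000 draws in each of 18 scenarios. Lost means at or above the floor with VI off and below it with VI on. A selection:

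| VI-OFF mean | Mean drop | Floor | Lost | Drop, all testable with VI off | Drop, still testable with VI on |
|---|---|---|---|---|---|
| 80 | 5 | 40 | 3.1% | 5.5 | 5.0 |
| 70 | 10 | 40 | 13.2% | 10.1 | 8.1 |
| 70 | 10 | 50 | 24.1% | 10.1 | 6.6 |
| 60 | 20 | 50 | 60.3% | 20.0 | 11.7 |

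A second set of assumptions (mean 65, SD 18; drop 5, 10 or 15, SD 10) gives losses of 10.3, 16.9 and 25.4% at a floor of 40, and 16.8, 26.5 and 37.9% at a floor of 50. For scale, one patient of 8 is 12.5%.

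In all 18 scenarios the mean drop is smaller among those still testable, so the direction of selection is stable. The drops are in quiet-speech points. They show who is selected and do not measure bias in the SRT, which cannot be computed from the documents.

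**5. Does worst-rank scoring work at this size?** Take 8 patients with 3 unobtainable VI-ON thresholds. The three share ranks 6, 7 and 8, so each gets (6 + 7 + 8)/3 = 7. The ranks are then 1, 2, 3, 4, 5, 7, 7, 7. Sign patterns whose opposite-direction rank sum is at most 3 are: none, {1}, {2}, {3}, {1,2}, which is 5 of 256, so two-sided p = 10/256 = 0.039. A sum of 4 adds {4} and {1,3}, giving 14/256 = 0.055. The test can again reach 0.05, but only if the other five patients largely point the same way.

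**The case against.** The strongest reply is that the interaction would not be missed. Exclusion is per outcome measure, aided CNC is recorded beside SPIN in both day-4 sessions, and 8.1.1 rests the CI-function comparison on CNC with the regular processor against the AMP. This stands. A reader might infer that the patient leaves the whole interaction comparison, but the documents support a loss from SPIN only.

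Second, the 40-50% level is an example of when the test is informative, not a run/do-not-run rule, and nothing says it is judged again with the VI on. This also stands, so the missing VI-ON score is an inference. The ambiguity is still worth closing, because one of its two readings produces the bias.

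Third, section 10 leaves the final imputation strategy to a definitive statistical plan that is not shown, and it promises that excluded cases will be described. Both are true. However, exclusion of structural missingness is already stated in the protocol, and imputation is reserved for data missing at random. The point therefore concerns a stated rule, not an absent one. Describing the cases helps but leaves the SPIN contrast selected.

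Fourth, Table 6 places the VI-ON measurement in the stimulation weeks, where the example schedule lists "DVA + dynamic CNC" and no SPIN; the baseline day lists none either. The fitting-day pair is thus not the tabulated contrast. That mismatch is real, but the floor applies wherever SPIN is measured with the VI on.

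Two further inferences are not supported. Section 8.3.2 lists alternative materials but does not say that a patient is moved to an easier one between conditions. Section 8.1.1 plans a follow-up comparison with a regular CI without defining the comparator, so one-sided selection of good CVI performers is not shown.

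**Conclusion.** The concern holds for SPIN only. If the minimum level is judged with the VI on, and an unobtainable threshold is treated as structurally missing, the stated rules remove the patients with most interference from the SPIN contrast and push it towards little interaction. Aided CNC would still show the loss in quiet.

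The direction rests on the text and on the reasoning in the working. The size is unknown: 3% to 60% lost reflects assumed distributions, and no figure for bias in dB can be given. A reader might take the simulated drops as the bias the trial would report. They are not, because CNC is not truncated and the SRT was not modelled.

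Severity is minor. SPIN is one of several outcomes for a secondary objective, and section 10 declares the trial exploratory with no population-wide claims.

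**What to change.** - **Section 8.3.2:** state that the minimum level of speech understanding in quiet is judged in the CI-only condition, and that a patient is tested with the same speech material in both conditions.
- **Section 10:** exempt an SRT that is unobtainable with the VI on, in a patient who passed the level with the CI only, from the structural-missingness exclusion. Score it as the worst rank in the paired signed-rank comparison.
- **Reporting:** give the number of such patients beside the aided CNC result, so that the two are read together.

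The cost is wording only, with no extra test or visit. The small downside is that SPIN is then summarised by ranks and medians and not by a mean difference in dB.

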#### 8.3.3. *Description of the device tests which will be conducted*

##### ***Auditory nerve response telemetry (ART) measurements***

ART measurements are a way to measure electrically evoked compound action potentials (ECAPs) of both vestibular and cochlear nerves with the CVI implant. ECAPs can be used to characterize nerve responses to electrical stimulation, which will offer insights into current spread throughout the inner ear and which may, among other things, be used as a guide to optimize the fitting of the CVI . To perform ART measurements, the CVI implant will be connected to a computer which runs CI fitting software. The measurement does not require any actions to be performed by the patient and takes around 5 minutes.

##### ***Impedance***

Impedance measurements act as a general safety check of the device. The test is performed to detect problems with the structural integrity of the electrodes and their ability to conduct electricity. This test is a routine test for CI implants and works the same for CVI implants. It is performed by connecting the implant to a computer and measuring the impedance of each electrode. The patient does not experience anything from this measurement, which takes around 2 minutes including set-up.

#### 8.3.4. *Description of the imaging techniques which will be used*

##### ***Magnetic resonance imaging (MRI)***

To assess anatomy and patency of the inner ear including the vestibular organ MRI imaging is used. The results of the MRI scan are used to decide whether the patient is fit for receiving a CVI. MRI is also a part of the regular pre-operative tests for receiving a CI.

##### ***Computed tomography (CT) scan***

In combination with the MRI scan, also a CT scan of the mastoid is clinically included in the pre-operative assessment for receiving a CI. During the pre-operative assessment for CVI implantation, we will use the same pre-operative CT to assess the individual anatomy and patency of the inner ear, and to plan a surgical approach for the CVI surgery. The pre-operative mastoid CT will also be fused with the per-operative 3DCT to assess electrode placement during the surgery. The radiation dose of a standard mastoid CT-scan is around 0.6mSv. See chapter 13.1.11 for further information on the total radiation exposure, the associated risks and justification for the risks.

##### ***Cone beam computed tomography (CBCT) scan***

A CBCT scan allows to check the position of the CVI electrodes in the cochlea and SCCs. In other clinics, this is often already a standard procedure after cochlear implantation. In our clinic, a post-operative CBCT scan is often included when clinical research is performed involving CI's ("ELEPHANT Trial" ABR 51559, "Bimodal Zoom" ABR 64874). Also within clinical care it is generally applied when problems or complaints occur with regular CI devices. The CBCT scan involves only a very small dose of radiation (0.05 mSv). See

chapter 13.1.11 for further information on the total radiation exposure, the associated risks and justification for the risks.

